**Figure 1 figure1:**
[figure not shown]
Study timeline.

At the beginning of each intervention period (weeks 0 and 5), participants reported to the Clinical Research Center on the OSU campus. At the Clinical Research Center, weight, vitals, and waist circumference were measured, sleep and diet questionnaires were answered, fasting indirect calorimetry was completed, a fasting blood draw was collected, and the meal challenge was administered with subsequent blood draws and indirect calorimetry measurements performed hourly for 5 hours. Additionally, cognitive function was measured both fasting and at 5 hours after the meal challenge, and any updates to medications and supplements were recorded. Each intervention period lasted 1 week and concluded with a study visit (week 1 and week 6). At the week 1 and week 6 visits, weight, vitals, and waist circumference were measured. A fasting blood draw was collected, cognitive function was measured, and updates to medications and supplements were obtained. There was a 4-week washout period between intervention periods. Figure 2 describes the measurements and information collected at each study visit. Participants were supplied with enough study snacks to consume 1 study snack per day until their next study visit. No study snacks were consumed during the washout period. At study visits, this study’s team verbally asked participants about adherence to consuming 1 study snack per day, changes to diet or activity, and changes to medications or supplements.

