### Outcomes

#### Cognitive Function

The primary outcome of the EFFECT study is the difference in postprandial cognitive score between control and walnut interventions. Additionally, the difference in change of premeal score at the start and end of the intervention period between the control and walnut interventions will be analyzed. To assess cognitive function, the National Institutes of Health Toolbox for the Assessment of Neurological and Behavioral Function Cognitive Battery (NIHTB-CB) was used, specifically the fluid cognition battery. The tests are fully automated and administered via an iPad (Apple Inc) with consistent program-derived instructions. Minimal practice effects and no floor or ceiling effects are seen with the NIHTB-CB [48-50].

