#### Meal Challenge

At weeks 0 and 5, participants received a high-kilocalorie meal challenge. The meal was approximately 900 kcal with 60 g of fat, 33 g of polyunsaturated fat for the walnut meal and 41 g of saturated fat for the control meal, 60 g of carbohydrates, and 37 g of protein; the meal consisted of a drink and the corresponding intervention period study snack. The macronutrient composition of the meals between the 2 study snacks was equivalent except for the saturated fat, monounsaturated fat, and polyunsaturated fat content. Participants had 20 minutes to consume the entire meal. To measure preprandial and postprandial metabolism, before consuming the meal (fasting) and each hour for 5 hours after consuming the meal, energy expenditure, blood pressure, and heart rate were measured, and venous blood samples and saliva samples were collected.

Energy expenditure was measured using indirect calorimetry (Ultima Series CPX, MGC Diagnostics). For the fasting indirect calorimetry, after arriving for their study visit, participants rested in a quiet, dim room on a hospital bed with the head of the bed at a 30° angle for 30 minutes before assessing energy expenditure over 25 minutes. For postprandial measurements, participants rested for 30 minutes in a hospital bed while being allowed to quietly read, use electronics, or sleep before a 20-minute indirect calorimetry measurement period. A heart rate monitor (FirstbeatTM Bodyguard 3, Firstbeat Technologies) was placed on the participant’s chest and abdomen at the start of the first resting period and measured their heart rate throughout this study’s visit. Fasting and postprandial blood pressure were measured using a blood pressure cuff.

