### Statistical Analysis

Postprandial cognitive test scores will be compared between the control and walnut group using a 2-sided paired *t* test to account for the cross-over design. To further adjust for covariates, a linear mixed effect model with subject-specific random intercept will be fit on postprandial test score with the following covariates: study group, preprandial test score at week 0 and 6, BMI, age, sex, education level, and depression score. The regression coefficient of this study’s group will be the adjusted difference in postprandial test score between this study’s groups. Potential carryover of treatment effects from the first treatment period to the second period will be assessed by including an interaction between treatment and period in the mixed-effect models. Significant interaction indicates the existence of a carryover effect, in which case we will only use data from the first treatment period to evaluate the treatment effect using a 2-sample *t* test and linear regression models. Analyses for the primary hypothesis will use participants who completed the entire study and will be based on an intention-to-treat principle, regardless of compliance and study group crossover. Sensitivity analyses will be conducted with multiple imputation on missing values for participants who do not complete the entire study. A linear mixed effect model with subject-specific random intercept will be fit on preprandial test score at week 1 and 6 with the following covariates: study group, preprandial test score at day 0 and 35, BMI, age, sex, and education level. The regression coefficient of this study’s group will be the adjusted difference in preprandial test score after a 7-day intervention between study groups. A linear mixed effect model with subject-specific random intercept will be fit on postprandial test score at weeks 0 and 5 with the following covariates: change in plasma sum of ALA+LA during 7-day intervention, BMI, age, sex, and education level. The regression coefficient of plasma sum of ALA+LA will measure the adjusted correlation between postprandial test score and change in plasma sum of ALA+LA.

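### The primary analysis is called intention-to-treat but is limited to completers of the whole study, a rule that, read literally, discards observed primary pairs when only week 6 is missed

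*Protocol article*

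**What the plan says.** The analysis set is fixed in one sentence of the Statistical Analysis section: "Analyses for the primary hypothesis will use participants who completed the entire study and will be based on an intention-to-treat principle", which continues "regardless of compliance and study group crossover". The next sentence deals with everyone else: "Sensitivity analyses will be conducted with multiple imputation on missing values for participants who do not complete the entire study".

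The Cognitive Function section says the primary outcome "is the difference in postprandial cognitive score between control and walnut interventions". The Meal Challenge section gives the timing: "At weeks 0 and 5, participants received a high-kilocalorie meal challenge". Study Timeline adds that at those visits "cognitive function was measured both fasting and at 5 hours after the meal challenge". The study then runs for one more week after the second challenge and ends with the week 6 visit, where cognition is tested once, without a meal challenge.

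The Randomization section places assignment after the week –1 visit and before the week 0 visit is completed. If carryover is declared, the Statistical Analysis section drops the second period and compares first-period data by a two-sample t test and linear regression.

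**The concern.** Two things are wrong with the rule as written.

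First, it contradicts its label. Assignment precedes the first meal challenge, so everyone who withdraws afterwards has been randomised, and restricting to finishers removes them. The added clause on compliance and crossover keeps non-adherent people only if they also finished. A report that followed this text would claim intention-to-treat for a completer analysis.

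Second, completion is judged at a visit that the primary outcome does not use. A participant whose week 0 and week 5 postprandial scores are both recorded has a usable pair, yet is removed for not attending week 6. The same rule reaches the carryover fallback. That is a between-sequence comparison resting directly on randomisation. Its outcome is recorded at week 0, but people could be removed for events up to six weeks later, after different exposures.

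At stake are an accurate description of the trial's main result, observed primary data discarded without need, and a selection on behaviour after randomisation that might not be neutral between sequences.

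**Working it through.** **Step 1. Which data does each analysis need, and what does the rule demand?**

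| Analysis | Scores needed | Demanded by the rule | Dropped although usable |
|---|---|---|---|
| Paired t test (primary) | Postprandial, weeks 0 and 5 | Completion through week 6 | People with both scores who miss only week 6 |
| Adjusted mixed model | At least one postprandial score plus covariates | Completion through week 6 | The same people, and those with one observed period |
| First-period fallback | Postprandial, week 0 | Completion through week 6 | Anyone with a week 0 score who leaves later |

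In no row does the outcome come from week 6.

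**Step 2. Reproduce the planned sample size.** Inputs from the Sample Size section: SD of the paired difference 11.0, difference 3.5, two-sided alpha 0.05, power 80%.

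Normal approximation: n = (SD × (z0.975 + z0.80) / difference)² = (11.0 × 2.8016 / 3.5)² = 77.53, rounded up to 78. The stated figure reproduces. The exact paired t test (noncentral t, 77 degrees of freedom, noncentrality 3.5/11.0 × √78 = 2.81) gives 79.2% power at 78; 80 pairs are needed to reach 80%.

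**Step 3. What does losing pairs cost?** The Recruitment section plans for 78 people, which is also the number in the power calculation. The article gives no dropout rate, so 5%, 10% and 15% are assumptions. Noncentrality is 3.5/11.0 × √n.

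| Assumed loss | Pairs | Power for 3.5 points | Difference detectable with 80% power |
|---|---|---|---|
| none | 78 | 79.2% | 3.53 |
| 5% | 74 | 77.1% | 3.63 |
| 10% | 70 | 74.7% | 3.74 |
| 15% | 66 | 72.1% | 3.85 |

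**Step 4. How much of that belongs to the rule?** Anyone who leaves before the week 5 challenge has no pair, and a paired t test cannot use that person under any definition of the set. Only people lost after the week 5 challenge are removed by the rule itself. Their number is not in the document. In this range, every two such pairs kept are worth about 1.1 to 1.3 percentage points of power (for example, 78.2% at 76 pairs against 77.1% at 74).

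**Step 5. What would single-period participants add to the mixed model?** For the treatment contrast, such a person carries roughly (1 − ρ)/2 of the information in a pair, where ρ is the within-person correlation. Assuming ρ = 0.8 gives (1 − 0.8)/2 = 0.10 of a pair; ρ = 0.5 gives 0.25. The gain is real but small.

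**The case against.** The strongest defence is that the restriction is open and partly repaired. The article states the completer set, explains that it means analysis as assigned whatever the adherence, and prespecifies multiple imputation for the rest. Imputation is valid under missing at random, so an analysis that brings non-completers back already exists. This stands as mitigation, but the headline estimate and its label remain those of a completer analysis.

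It can also be said that a condensed article leaves the working definition of a completer to the full protocol or SAP. That weakens the week 6 argument, which depends on a literal reading. It does not touch the label, since both halves of the contradiction are printed in one sentence.

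A third defence is that the adjusted model lists the fasting score at weeks 0 and 6, so week 6 would be needed. This does not hold. The challenges are at weeks 0 and 5, the same section uses days 0 and 35 for the start-of-period fasting scores in another model, and the paired t test has no covariates.

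Several stronger readings are tempting but not supported:

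- A reader might infer that this rule takes power down to 72.1%. That figure describes total loss of pairs at an assumed rate, most of which a paired test may suffer anyway.
- A reader might infer that the primary contrast is biased. That would need week 6 attendance to be related to the within-person difference between snacks, and nothing in the document shows this.
- A reader might infer that unequal exclusions between sequences let a period effect through. The paired t test and the main covariate list do omit period. But the carryover check includes a treatment-by-period interaction, and the article expects minimal practice effects, so this is a possibility only.
- A reader might infer that the mixed model must replace the paired t test. That is a larger change to the test on which the sample size rests, and a set requiring at least one postprandial score is itself a modified intention-to-treat set.

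**Conclusion.** The point holds as a wrong rule with a wrong label. The stated primary set is a completer set, and followed literally it discards complete week 0 and week 5 pairs, and first-period data in the fallback, because of later non-attendance. The label conflict is certain from the text. The week 6 exclusion rests on taking the completion wording at face value.

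The consequences are bounded but not measurable from the document. The loss of pairs due to week 6 alone could be zero, and neither the size nor the direction of any bias can be calculated, because no dropout rate or reasons are given. The planned 78 is not in error as a calculation. The planned imputation limits the damage, but the matter should be settled before the primary analysis is run.

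**What to change.** Replace the sentence that defines the analysis set with the following content:

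- **Primary paired t test:** every randomised participant with both the week 0 and week 5 postprandial scores, analysed in the sequence assigned, regardless of adherence or week 6 attendance.
- **Adjusted mixed model:** all randomised participants with at least one postprandial score. Reconcile the fasting covariate printed as weeks 0 and 6 with the week 0 and week 5 challenges, so that the model does not depend on week 6.
- **First-period fallback:** all randomised participants with the first-period postprandial score, whatever happened later.
- **Sensitivity analysis:** keep multiple imputation, for randomised participants without a pair.
- **Label:** describe the primary set as randomised participants with both primary scores, not as unqualified intention-to-treat. Report by sequence how many were randomised, how many had a pair, and how many missed only week 6.

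The cost is wording and a few counts, with no new data. Because the research team is not blinded and final visits were projected for July 2025, the change needs a dated, documented justification before analysis, so that it cannot be read as driven by the results.

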**Objective:**

The primary objective of the Essential Fats for Enhancing Cognitive Thinking study is to determine the impact of walnuts on postprandial cognitive function in adults with SCI. Secondary objectives include assessing the impact of daily walnut consumption for 1 week on cognitive function and erythrocyte fatty acids. Exploratory objectives include understanding the effect of walnut consumption on microbiota and intestinal inflammation.

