**Methods:**

In this 7-week single-blind randomized crossover design study, 78 adults with SCI consumed 1 study snack per day, consisting of walnuts or a chocolate-style snack for 1 week, with a 4-week washout period between. Before consuming each study snack, participants underwent a meal challenge that included this study’s snack. Before randomization, participants completed a 1-week run-in period to become acclimated to consuming 1 study snack per day. A registered dietitian nutritionist counseled participants on incorporating this study’s snack into their diet while maintaining their body weight. Participants were blinded to which snack was the treatment and which was the control. Dietary intake and physical activity were measured with 24-hour recalls. Cognitive function was measured using the National Institutes of Health Toolbox for the Assessment of Neurological and Behavioral Function Cognitive Battery, both pre- and postprandially, as well as after 1 week of study snack consumption. Stool samples were collected weekly, except during the washout period, to measure microbiota α-diversity, β-diversity, and butyrate. Additionally, fasting blood samples, weight, and waist circumference were obtained at each study visit.

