#### Biochemical Markers

Glycated hemoglobin was measured using a finger stick. Erythrocyte and PBMC fatty acids will be analyzed. PBMC lipids will be extracted using methanol and chloroform (1:2 v/v) [57] and methylated using 5% hydrochloric acid in methanol [58] as previously described [59]. Erythrocyte fatty acid methyl esters will be prepared using 14% boron trifluoride in methanol and hexane [60] as previously described [61,62]. Gas chromatography with a 30-m Omegawax TM 320 fused silica capillary column (Supelco) will be used to analyze the fatty acid methyl esters. Standards for fatty acid methyl esters (Matreya, LLC and Nu-Check Prep Inc) will be used to determine retention times of fatty acids in the samples as previously described [63].

From blood collected at fasting and postprandial time points, lipid panels were measured at the OSU Wexner Medical Center Hospital Lab. Glucose will be measured using the Glucose Autokit (FUJIFILM Healthcare Americas Corporation), and insulin levels will be measured using the Meso Scale Diagnostics kit. Fasting glucose and insulin levels will be used to calculate estimated insulin resistance using the homeostatic model assessment of insulin resistance [64]. Markers of inflammation, including fasting and postprandial tumor necrosis factor alpha, tumor necrosis factor receptor 2, C-reactive protein, interleukin-6, and soluble intercellular adhesion molecule-1, will be measured at weeks 0 and 5. Fasting soluble CD14, oxidized low-density lipoprotein, and lipopolysaccharide binding protein will also be measured. Tumor necrosis factor α, tumor necrosis factor receptor 2, soluble intercellular adhesion molecule-1, C-reactive protein, interleukin-6, and lipopolysaccharide binding protein will be measured using a highly sensitive Meso Scale Diagnostics kit, and soluble CD14 and oxidized low-density lipoprotein will be measured by ELISA kits (R&D Systems and Mercodia, respectively). Lipopolysaccharide will be measured using Kinetic-QCL, Kinetic Chromogenic LAL Assay, or ELISA LifeSpan BioSciences. Markers of oxidative stress, 4-hydroxynonenal and malondialdehyde, will also be measured by multiplex methods as previously reported [54,65-68].

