A linear mixed effect model with subject-specific random intercept will be fit on the change of endotoxemia during the 7-day intervention with the following covariates: study group, BMI, age, sex, and education level. The regression coefficient of this study’s group will be the adjusted difference in the reduction of endotoxemia between this study’s groups. β*-*diversity of the microbiome community at days 7 and 42 between all pairs of participants will be calculated using the Bray-Curtis dissimilarity measure. Nonmetric multidimensional scaling ordination will be computed, and nonmetric multidimensional scaling plots will be generated to visualize the difference in β-diversity between study groups. Permutation-based ANOVA will be used to compare the β-diversity between study groups. Operational taxonomic units (OTU) abundance will be compared between study groups using paired *t* tests for each OTU, and the *P* values will be adjusted by the Benjamini-Hochberg procedure [76] to control for false discovery rate. A linear mixed effect model with subject-specific random intercept will be fit on postprandial test score with the following covariates: change of endotoxemia during the 7-day intervention, change of OTU abundance during the 7-day intervention, BMI, age, sex, and education level. As the number of OTUs will be very large, exceeding the sample size, a LASSO (Least Absolute Shrinkage and Selection Operator) penalty [77] will be included in the regression model to select significant covariates.

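### Two models relate the week 0 and 5 postprandial score to biomarker changes over the following 7 days and omit study group, so their coefficients cannot show a biomarker effect on that score

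*Protocol article*

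**What the plan says.** **Outcome timing.** The Meal Challenge section states: "At weeks 0 and 5, participants received a high-kilocalorie meal challenge". Study Timeline places these visits at the start of each period ("At the beginning of each intervention period (weeks 0 and 5), participants reported to the Clinical Research Center on the OSU campus") and says that "cognitive function was measured both fasting and at 5 hours after the meal challenge". The Abstract agrees on the order: "Before consuming each study snack, participants underwent a meal challenge". Each period closes one week later, at week 1 or week 6. The score that Statistical Analysis uses at those visits is a preprandial one.

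**Models.** Statistical Analysis has two regressions that link biomarkers to the postprandial score:

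- The fatty-acid model is "fit on postprandial test score at weeks 0 and 5 with the following covariates: change in plasma sum of ALA+LA during 7-day intervention", plus BMI, age, sex and education. Its coefficient is described as an adjusted correlation.
- The endotoxemia and microbiome model takes the postprandial score, with no visit named, and uses "change of endotoxemia during the 7-day intervention, change of OTU abundance during the 7-day intervention" plus the same four personal covariates, with a LASSO penalty.

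Study group is a covariate in neither. It is a covariate in the neighbouring models for the week 1 and 6 fasting score and for the change in endotoxemia.

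**Fatty-acid matrix.** Biochemical Markers says "Erythrocyte and PBMC fatty acids will be analyzed". The Abstract's secondary objective is "assessing the impact of daily walnut consumption for 1 week on cognitive function and erythrocyte fatty acids". Plasma ALA+LA appears only in the fatty-acid model.

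**The concern.** The Introduction offers ALA and LA, endotoxemia and the microbiota as possible routes from walnuts to cognition. The Discussion promises to examine how microbiota and urolithins relate to postprandial cognition. Readers will look to these two regressions for that evidence.

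A change that is complete a week after a test cannot have produced the test result. Because the snack may move both the score and the biomarker, a model without study group can also return a clear coefficient when the two have no other connection. A significant result would then repeat the walnut-control contrast under a biomarker's name. In the LASSO model, OTUs that shift with the snack could be selected as stand-ins for snack assignment.

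The matrix question is separate and smaller: as written, the fatty-acid covariate does not match any fatty-acid assay listed.

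**Working it through.** **1. Timeline.** Day numbers follow Statistical Analysis, which uses days 0, 7, 35 and 42.

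| | Period 1 | Period 2 |
|---|---|---|
| Fasting blood draw and fasting score | day 0 | day 35 |
| Postprandial score (outcome) | day 0 + 5 h | day 35 + 5 h |
| 7-day change (predictor) runs | day 0 to 7 | day 35 to 42 |
| Predictor complete after outcome by | 7 × 24 − 5 = 163 h | 163 h |

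The lag is 163/24 = 6.8 days in both periods. For the fatty-acid model this is explicit. For the endotoxemia and OTU model it follows because no postprandial score is described at any other visit.

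**2. The plan's own figures.** The next step borrows the sample-size inputs: SD of the paired difference 11.0, difference 3.5, 2-sided 5%, 80% power. The normal approximation gives n = (11.0 × (1.960 + 0.842)/3.5)² = 77.5, so 78, as stated. (The exact t calculation gives 79.2% power at 78; nothing here depends on that.)

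**3. What omitting study group does.** Assume that walnuts raise the score by 3.5, that walnuts shift the biomarker change by s SD, and that the biomarker has no other link to the score. Take the biomarker noise as SD 1 in each period, independent between periods.

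Within a person, the walnut-minus-control differences are:

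- score: mean 3.5, SD 11
- biomarker: mean s, variance 1 + 1 = 2

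Without study group, the within-person slope tends to 3.5·s/(s² + 2):

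- s = 0: 0
- s = 1: 3.5/3 = 1.17 points per SD
- s = 2: 7/6 = 1.17 points per SD

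The true link is zero throughout. The between-person slope is also zero, so a random-intercept model gives a value between 0 and 1.17. With study group included, the expected slope is 0.

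**4. Simulation.** Settings: 78 participants with both periods, between-person SD 11, residual SD 11/√2 per period (so the paired-difference SD is 11), a random-intercept model, and 300 runs per setting. BMI, age, sex and education were left out.

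| Walnut shift in biomarker | Rejects at 5%, no study group | Rejects at 5%, study group added |
|---|---|---|
| 0 SD | 4.7% | 5.0% |
| 1 SD | 29.7% | 3.3% |
| 2 SD | 58.3% | 5.3% |

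The Monte Carlo standard error is √(0.05 × 0.95/300) = 1.3 points near 5% and √(0.58 × 0.42/300) = 2.8 points near 58%. The table measures the missing study-group term only. Time order needs no simulation: adding study group removes the spurious rejections but leaves the predictor later than the outcome.

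**5. Matrix.** The model uses plasma. The assay list has erythrocytes and PBMC. The objective names erythrocytes, and the limitations section uses erythrocyte profiles for adherence. The model is the only place where plasma fatty acids occur.

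**The case against.** The strongest reply is that the text claims no more than an adjusted correlation, in secondary or exploratory work. That stands: the models can be computed, and the statistical section asserts no mediation. A stable trait, such as how a person responds to a fat load, could drive both the acute score and the week's change, and that is a legitimate thing to explore. The window also opens with a fasting draw before the meal, so the score falls early inside the window and not ahead of all of it. None of this lets the coefficient show that the change acted on the score, and none of it removes the influence of snack assignment.

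Four stronger readings are tempting, and the article does not support them:

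- *A reader might infer that the microbiome, endotoxemia and fatty-acid objectives cannot be answered.* Those objectives concern the effect of walnuts. Endotoxemia, β-diversity and OTU abundance have their own group comparisons, none of which uses the postprandial score.
- *A reader might infer that erythrocyte fatty acids will go unanalysed.* The article gives no model for them, but the full analysis plan is not shown and may.
- *A reader might infer that plasma is simply a slip for erythrocyte.* PBMC is also listed, venous blood is drawn, and the assay text is not exhaustive: butyrate and urolithins are to be studied without a described assay. The mismatch calls for reconciling and no more.
- *A reader might take the 30% and 58% as the cost of the time order.* They come from omitting study group, under assumed values.

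**Conclusion.** The point holds for both regressions of the postprandial score on 7-day changes: explicitly for ALA+LA, and by clear inference for endotoxemia and OTU abundance. The predictor is complete about 7 days after the outcome, and study group is missing. As written, neither coefficient can show that the biomarker change influenced the score, and either may be produced by snack assignment alone.

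How often that would happen depends on the true walnut effects on score and biomarker, which the article does not give. Under the assumptions above, false rejection runs from about 5% with no biomarker shift to about 58% with a 2 SD shift.

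The primary paired t test, the sample size and the separate biomarker group comparisons are untouched. This should be corrected, but it does not threaten the trial's main result.

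**What to change.** 1. Relate the 7-day changes (ALA+LA, endotoxemia, OTU abundance) to the fasting score at weeks 1 and 6, adjusted for the same-period fasting score at weeks 0 and 5, study group and period, alongside the personal covariates already listed.
2. For the postprandial score, use only predictors measured before or during that day's challenge, such as the fasting marker at weeks 0 and 5 or, where assayed, the fasting-to-postprandial response. Include study group and period.
3. In the LASSO model, leave study group and period unpenalised so that they cannot be dropped.
4. If the pairing as written is kept, add study group and report the result only as a non-mechanistic association.
5. Name the visit in the endotoxemia and OTU model.
6. Reconcile plasma ALA+LA with the erythrocyte and PBMC assays and the erythrocyte objective, or describe a plasma assay.

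**Cost.** This is mainly a rewrite of two model statements. Fasting blood, cognitive scores and stool are collected at weeks 0, 1, 5 and 6, so no new visit is needed. The article does not say at which visits every marker is assayed, so that should be confirmed. The fasting-score models address the 7-day effect and not the postprandial one, which is a different question. Adding study group may widen the confidence interval of the biomarker coefficient, because part of the biomarker's variation is the snack contrast.

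### The two models relating marker changes to postprandial score omit the same-visit fasting score, so their marker slope mixes within-person and between-person association and loses precision

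*Protocol article*

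**What the plan says.** All the models concerned are in the protocol article, Methods, Statistical Analysis.

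- **ALA+LA model.** "A linear mixed effect model with subject-specific random intercept will be fit on postprandial test score at weeks 0 and 5", with "covariates: change in plasma sum of ALA+LA during 7-day intervention, BMI, age, sex, and education level". Its marker coefficient "will measure the adjusted correlation between postprandial test score and change in plasma sum of ALA+LA".
- **Endotoxemia/OTU model.** Also a random-intercept model of postprandial score, with "change of endotoxemia during the 7-day intervention, change of OTU abundance during the 7-day intervention, BMI, age, sex, and education level" and a LASSO penalty.
- **Adjusted group model of postprandial score.** Its covariates are "study group, preprandial test score at week 0 and 6, BMI, age, sex, education level, and depression score".
- **7-day model of preprandial score.** Its covariates are "study group, preprandial test score at day 0 and 35, BMI, age, sex, and education level".

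The Study Timeline section says that at the start of each intervention period (weeks 0 and 5) "cognitive function was measured both fasting and at 5 hours after the meal challenge". The score that the two marker models leave out is therefore available at the visits they analyse.

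**The concern.** The fasting test separates how a person usually performs, and how they are on that day, from performance after the meal. The plan uses a preprandial score when it compares snacks with covariate adjustment, but not when it relates markers to the postprandial score.

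This matters more for a marker than for the snack comparison. Each participant receives both snacks, so study group does not differ between people on average, and stable ability cannot enter its coefficient in complete data. Marker change does differ between people. A random intercept is assumed to be independent of the covariates, so it does not remove a link between ability and marker change. If, say, more able participants ate the snack more reliably and so had larger ALA+LA rises, part of the slope would reflect an association present before the meal.

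At stake are the reading and the precision of the marker associations, which are secondary or exploratory.

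**Working it through.** **The plan's own figure.** No figure is given for the marker models. The Sample Size section's figure for the primary comparison reproduces: n = (11.0 × (1.960 + 0.842) / 3.5)² = 8.806² = 77.5, so 78. (The noncentral t gives 79.2% power at 78, and n = 80 for 80%.) Nothing below changes this.

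**Inputs for the ALA+LA model**

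- From the article: 78 participants with two visits each, and SD of the paired difference 11.0. The visit-level variance is 11.0² / 2 = 60.5.
- Assumed: total SD 15, so the stable between-person variance is 225 − 60.5 = 164.5.
- Assumed: correlation r of 0.3 to 0.5 between the visit-specific parts of the fasting and postprandial scores.
- Assumed: marker change = group × (1 + 0.7 × adherence) + noise of SD 0.5, with adherence standardised and no true association with the score.
- REML random-intercept fits on simulated datasets.

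**Precision, with ability and marker unrelated.** The slope's SE is about 0.85 as written. With the fasting score added it is:

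- r = 0.3: 0.73, a cut of (0.85 − 0.73) / 0.85 = 14%, worth (0.85 / 0.73)² = 1.36 times the participants.
- r = 0.5: 0.65, a cut of (0.85 − 0.65) / 0.85 = 24%, worth (0.85 / 0.65)² = 1.71 times the participants.

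**Bias, as written.** A nominal 5% test rejects about 5% of the time when adherence and ability are uncorrelated, 7% at correlation 0.3 and 12% at 0.5. The spurious slope at 0.5 is 0.53 to 0.69 (marker noise SD 0.5 or 0.7).

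**Sensitivity of the bias.** A second set of simulations correlated the stable part of the marker directly with ability (0, 0.3 or 0.5) and took between 50% and 85% of the score variance as stable. The rejection rates were:

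| Setting | Without fasting score | With fasting score |
|---|---|---|
| Correlation 0 | about 4–7% | about 4–7% |
| 0.3–0.5, snack shifts marker by 2 SD | 7–40% | 6–18% |
| 0.3–0.5, snack does not shift marker | 8.5–91% | 6–36% |

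The size of any bias is thus governed by quantities the article does not give.

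**What each remedy does, at correlation 0.5.** The fasting score alone leaves a spurious slope of about 0.15 to 0.30. Splitting marker change into participant mean and visit deviation brings the within-person slope to about 0, with about 5% rejection.

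**Precision after the split.** The within-person slope uses only the difference between a person's two visits. The mean square of the marker difference is 1 + 0.7² + 2 × 0.5² = 1.99, and the score difference has variance 121. Hence SE = √(121 / (78 × 1.99)) = 0.883. Adding the fasting score multiplies this by √(1 − r²):

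- r = 0.3: 0.883 × 0.954 = 0.842, which is 1% below 0.85.
- r = 0.5: 0.883 × 0.866 = 0.765, which is 10% below 0.85.

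Much of the 14% to 24% gain therefore comes from using between-person marker differences more fully, and those are the part exposed to confounding.

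**The case against.** **The plan states its own target.** It is a correlation with the postprandial score, not with the change from fasting. The primary outcome is also a postprandial level, and the primary paired *t* test has no fasting adjustment. This stands in part: a level is a legitimate outcome, and the plan does not claim to model the response from fasting. But the paired test removes stable ability by differencing, whereas the marker slope does not. The comparison with the primary test does not settle the matter.

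**A reader might infer that these models measure general ability and not the response to the meal.** The article does not support that. With two visits per person and a random intercept, the slope is a weighted mix of both.

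**A reader might also infer that false positives are known to be inflated.** They are not. Inflation needs an ability–marker correlation that the article does not report, and with none there is no bias. Simulated rates of about 11% and 21–24% (at correlations 0.3 and 0.5) can be obtained, but from a model that includes study group, which neither marker model contains.

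**The simulations cover one marker and a Wald test.** They do not carry over to the LASSO model. This stands. There the point rests on the covariate list alone.

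**The postprandial test precedes the 7-day marker change.** This also stands. Adjusting for the fasting score does not alter that order or make the slope causal.

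**Conclusion.** The point holds as one of interpretation and efficiency. Both marker models omit a score collected at the same visits, whose counterpart enters the other two cognitive mixed models. This is not detail left to a fuller document, because the article sets out the covariate lists.

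- **Precision.** The ALA+LA slope's SE is about 14% to 24% smaller with the fasting score. This rests on the assumed total SD of 15, within-visit correlation of 0.3 to 0.5 and marker model, and requires no confounding.
- **Bias.** It is possible but undocumented: about 7% rejection at correlation 0.3 and 12% at 0.5 in the main setup, with a wide range under other assumptions.
- **Remedy.** The fasting score alone would reduce such bias, not remove it. Removing it takes the marker split, which gives up most of the precision gain.

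No size can be put on the effect in the endotoxemia/OTU model. The primary paired *t* test and the sample size of 78 are untouched. The change is worth making but is not critical.

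**What to change.** 1. Add the same-visit preprandial score (weeks 0 and 5) to both marker models, entered as the participant mean plus the visit deviation. In the LASSO model, leave these two terms unpenalised so that selection cannot drop them.
2. In the ALA+LA model, also split the marker change into participant mean and visit deviation. Report the within-person slope as the association, described as an association with the postprandial score given the fasting score.

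The cost is a few sentences of analysis wording and no new data. The fasting score takes two degrees of freedom in each model, and the marker split one more in the ALA+LA model. The price of the split is that the SE gain over the model as written shrinks to about 0 to 10%. The article describes these analyses in the future tense, so the wording should be fixed before results are examined.
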